### Control group

The control group will participate in a web-based intervention with no sexual health information.

Participants in both groups will be afforded unlimited access to their allocated content over the 6-month study period, but that content will be available only to participants who log in with a registered email address and password. After the study period, the content accessed by the intervention group will be made available to the control group subjects as well.

### Study outcomes

The study outcomes will be measured in both groups at baseline (T0) and at 3 months (T1) and 6 months (T2) after baseline. The primary outcome will be the frequency of condomless anal sex in the past 3 months, based on the recommendation of a systematic review of 56 studies [42]. The secondary outcomes will be the frequency of group sex and chemsex, self-efficacy and attitudes toward condom use, and frequency of HIV and other STI testing.

Data on these outcomes will be collected and evaluated as follows.
Frequency of condomless anal sex in the past 3 months is measured by a self-reported item at baseline, 3-month follow-up and 6-month follow-up.Frequency of group sex in the past 3 months is measured by a self-reported item at baseline, 3-month follow-up and 6-month follow-up.Frequency of chemsex in the past 3 months is measured by a self-reported item at baseline, 3-month follow-up and 6-month follow-up.Self-efficacy in condom use is measured by the validated traditional Chinese version of the Condom Self-Efficacy Scale at baseline, 3-month follow-up and 6-month follow-up [43].Attitudes towards condom use is measured by the UCLA Multidimensional Condom Attitudes Scale at baseline, 3-month follow-up and 6-month follow-up [44].Frequency of HIV testing in the past 3 months is measured by a self-reported item at baseline, 3-month follow-up and 6-month follow-up.Frequency of STI testing in the past 3 months is measured by a self-reported item at baseline, 3-month follow-up and 6-month follow-up.

Finally, participants’ sociodemographic characteristics (e.g. age and education level), sexual histories (e.g. age of sexual initiation), reported use of pre-exposure prophylaxis and their patterns of dating app usage will be collected.

At 6-month follow-up (T2), participants will be asked whether they find the web-based information useful and are satisfied with the web-based information.

Table 1 shows the SPIRIT diagram for the schedule of enrolment, interventions, and assessments.

**Table 1 Tab1:** SPIRIT diagram for the schedule of enrolment, interventions, and assessments

	Study period				
	Enrolment	Allocation	Post-allocation		Close-out
Timepoint	***-t***_***1***_	0	***T0***	***T1***	***T2***
**Enrolment:**					
**Eligibility screen**	X				
**Informed consent**	X				
**Allocation**		X			
**Interventions:**					
**Intervention group**			X	X	
**Control group**			X	X	
**Assessments:**					
**Primary outcome and secondary outcomes**^a^	X				
**Primary outcome and secondary outcomes**^a^				X	X

Note: The study outcomes will be measured in both groups at baseline and at 3 months (T1) and 6 months (T2) after baseline

^a^ The primary outcome is the frequency of condomless anal sex in the past 3 months. The secondary outcomes are the frequency of group sex and chemsex, self-efficacy and attitudes toward condom use, and frequency of HIV and other STI testing

### Data analysis

The continuous outcomes in the intervention and control groups at the 3- and 6-month follow-ups will be evaluated using an independent t-test, and then compared using a linear mixed-effects model with the intervention group as the covariate. Subject as random effect will be included in the model if significant. In case of a baseline imbalance, additional analysis will be performed, with adjustment of the variables found to be imbalanced. The intention-to-treat principle will be adopted, and all study subjects will be included in the analysis as randomised. The baseline-observation-carried-forward approach will be used for missing values at the 3- and 6-month follow-ups. Model adequacy will be verified by examining the standardised residuals for normality and constant variance.

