### The use of dating apps: an emerging risk factor in sexual health

The use of dating apps is considered a factor leading to the rapid spread of STIs, including HIV [20, 21]. In Hong Kong, it has been reported that it is not uncommon for dating apps to be employed in search of sexual activities [22]. A report also claimed that the abundance of dating apps has exacerbated the problem of recreational drug use during sexual contexts (known as ‘chemsex’) [23]. Furthermore, there has been a significant increase in police reports of sexual assaults and violence related to dating app use in the United Kingdom [24]. Several empirical studies have explored the association between dating app use and risky sexual behaviours [25, 26].

A systematic review summarising 13 articles on the use of dating apps and associated risky sexual behaviours among the lesbian, gay, bisexual and transgender populations, which found that dating app users tended to engage in more high-risk sexual behaviours than nonusers, including having sex with multiple partners and engaging in condomless anal sex [26]. This review affirms the need to promote safe sex and positive sexual health messages to dating app users*.* A study was conducted among university students in Hong Kong found that dating apps users were more likely than nonusers to have multiple sexual partners and condomless sex with more sexual partners, use condoms inconsistently, engage in casual sex, and sexual abuse [27–29]. Another study on MSM dating app users in Hong Kong found that about 30% of participants had had more than three sexual partners, 25% had engaged in condomless anal sex with casual partners, 20% had had condomless anal sex with internal ejaculation, 15% had used alcohol in conjunction with sex in the past 6 months, 13% had had group sex, 8% had had chemsex [30]. These alarming findings indicate the urgent need for interventions to encourage better and safe sexual health in Hong Kong dating app users.

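### Skewed frequency outcomes, the primary included, are given only a t-test and a normal linear model, with a residual check that has no planned alternative

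*Protocol article*

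**What the plan says.** Under Study outcomes, the primary endpoint comes from one item: "Frequency of condomless anal sex in the past 3 months is measured by a self-reported item at baseline, 3-month follow-up and 6-month follow-up". Group sex, chemsex, HIV testing and STI testing are each measured in the same way. Only the two condom measures, self-efficacy and attitudes, are scale scores.

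Under Data analysis there is one route: "The continuous outcomes in the intervention and control groups at the 3- and 6-month follow-ups will be evaluated using an independent t-test". The same sentence goes on to the model, so that these outcomes "will be evaluated using an independent t-test, and then compared using a linear mixed-effects model with the intervention group as the covariate". No other covariate is named for that model. Baseline variables enter only in an additional analysis, and only if they turn out to be imbalanced. The section ends: "Model adequacy will be verified by examining the standardised residuals for normality and constant variance". It does not say what happens if that check fails.

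The sample size section also rests on an independent t-test, with an effect size of 0.3. The Background section reports, for local men using dating apps, that "25% had engaged in condomless anal sex with casual partners" and that "13% had had group sex, 8% had had chemsex".

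**The concern.** Frequencies of this kind are usually non-negative and right-skewed, and many men report none. The plan treats them as continuous, sets a normality and constant-variance check that such data will very probably fail, and then stops. The analyst would have to choose a model for the primary endpoint after seeing the outcome data, in a trial that the Study design section describes as non-blinded. Pre-specification is meant to prevent that choice.

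Two further costs follow. A mean difference in a rare behaviour rests on a small group of active men: roughly one man in ten for group sex and chemsex. And an effect of 0.3 standard deviations on a skewed frequency can mean a very large behavioural change, which the plan does not bring out.

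**Working it through.** **Inputs from the article.** Effect size 0.3, 80% power, significance level 0.05, 175 per group, 12.4% attrition, 1:1 allocation. Background prevalences are 25% (condomless anal sex, casual partners only), 13% (group sex) and 8% (chemsex). The recall period for these appears to be 6 months; a 3-month period would give at least as many zeros.

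**Step 1: the plan's own figure.** n per group = 2(1.960 + 0.842)² / 0.3² = 174.4, so 175. Then 350 / (1 − 0.124) = 399.5, so 400. Both reproduce (two-sided test).

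**Step 2: zeros implied by the background figures.** 1 − 0.25 = 75%, 1 − 0.13 = 87%, 1 − 0.08 = 92%. The 75% covers casual partners only, so it does not give the zeros on the primary outcome, which may be fewer. No figure is given for HIV or STI testing.

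**Step 3: what 0.3 SD means on such a count.** *Assumed* model: a share p reports any event. Among them the count is 1 plus a negative binomial with mean m − 1 and shape k, using (m, k) = (3, 1) or (6, 0.7). The variance of the positive part is v = (m − 1) + (m − 1)²/k, which is 6 or 40.7. Then mean = pm, SD = √[p(v + m²) − (pm)²], and the relative reduction equal to 0.3 SD is 0.3 × SD / mean.

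Example, p = 0.5 and m = 3: mean 1.5; SD = √(0.5 × 15 − 2.25) = 2.29; reduction = 0.3 × 2.29 / 1.5 = 46%.

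| Share with any event | Mean (m = 3, m = 6) | SD | Reduction equal to 0.3 SD |
|---|---|---|---|
| 50% | 1.50, 3.00 | 2.29, 5.42 | 46%, 54% |
| 25% | 0.75, 1.50 | 1.79, 4.11 | 71%, 82% |
| 13% | 0.39, 0.78 | 1.34, 3.06 | 103%, 118% |
| 8% | 0.24, 0.48 | 1.07, 2.43 | 134%, 152% |

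A value above 100% cannot be reached at the control-group SD. The 13% and 8% rows concern secondary outcomes, for which the plan does not claim that effect.

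**Step 4: would the check fail?** The same model was simulated with 175 per arm, taking residuals from the group means.
- Shapiro-Wilk rejected normality in every simulated trial in all eight settings. Skewness ran from 2.4 (50% with any event) to 8.2 (8%).
- A 30% fall in the share with any event cut the SD to 0.84-0.89 of control, so constant variance fails when the intervention works.
- The t-test's type I error was 4.3-5.0%.
- Its power for that 30% reduction was 38-50% at 50% prevalence, 20-25% at 25%, and 8-15% at 8-13%.

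**Step 5: where can power be recovered?** Two further sets of simulated trials used gamma-frailty Poisson counts with structural zeros, 175 per arm and a true 40% reduction. All parameters are assumed. Set A had a baseline-follow-up correlation of about 0.67-0.77; set B had 0.76-0.82.

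| Power | Set A: 36 / 53 / 66% zeros | Set B: 34 / 50 / 62% zeros |
|---|---|---|
| t-test | 79 / 50 / 36% | 86 / 71 / 50% |
| Negative binomial, no baseline | 80 / 54 / 43% | 87 / 73 / 55% |
| Negative binomial, log baseline | 97 / 85 / 71% | 99 / 92 / 83% |
| Linear with baseline, robust errors | not reported | 99.6 / 98 / 91% |

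The log link alone adds 1, 4 and 7 points in set A and 1, 2 and 5 in set B. Adding baseline to the negative binomial gains 17, 31 and 28 points in set A and 12, 19 and 28 in set B. The type I error of the baseline-adjusted linear model in set B was 3.6-5.0%.

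**The case against.** The strongest reply is that a randomised comparison of two means is robust here. With 175 per arm and equal allocation, neither skewness nor unequal variance disturbs the type I error, and the mean difference is a valid average effect. This stands. A reader might infer that the t-test would give false positives, or that the linear model needs the same absolute reduction in every man; neither is so.

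A reader might also infer that a count model would rescue power. It would not by itself. Nearly all the gain comes from baseline, and in set B a linear model with baseline did at least as well as the negative binomial.

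It can further be said that the item's response format is not given, so counts are an inference, and that mostly-zero data are documented only for group sex and chemsex. The first point stands, though ordered categories would not suit a normal model either. The second stands too: eligibility requires men to be sexually active, and the 25% leaves out regular partners. But the check failed in simulation with only half the values at zero.

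Finally, a fallback could sit in an analysis plan that is not shown, and the word continuous might be meant for the two scales alone. The difficulty lies in what the article does fix: a t-test in both the sample size and the analysis sections, and a check with no consequence attached. If continuous meant only the scales, the primary endpoint would have no stated analysis.

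**Conclusion.** The point holds as a mismatch between skewed frequency outcomes and the one analysis stated, joined to an adequacy check that will very probably fail and leads nowhere. The cost is power, interpretability and an unplanned model choice on the primary endpoint. It is not inflated type I error, and the sample size arithmetic is correct for its stated inputs.

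The size depends on assumptions. If half the men report any condomless anal sex, 0.3 SD corresponds to a fall of about 46-54% in the mean count; if a quarter do, 71-82%. The article gives no mean, dispersion or response format for the primary outcome, so these are illustrations and no replacement sample size can be derived. The check was simulated on residuals from group means, not from the full mixed model. This is an inexpensive improvement worth making before outcome data are seen; it does not invalidate the trial.

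**What to change.** For the primary outcome, pre-specify one baseline-adjusted analysis with robust standard errors, clustered by participant across the two follow-ups, that does not depend on residual normality. Either of these serves:
- a negative binomial model or log-link GEE with log(baseline + 1) as covariate, reporting a rate ratio; or
- a linear model with baseline as covariate, reporting a mean difference.

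Name the choice before outcome data are seen, state the response format of the item, and say what change in frequency the 0.3 planning effect represents. Drop the residual check as a gate on the primary analysis, or state what follows if it fails.

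For group sex and chemsex, keep frequency as the stated outcome and add a pre-specified any-versus-none analysis alongside it. Replacing frequency outright, or doing so for HIV and STI testing, would change the stated targets. Keep the linear model, with baseline added, for the two condom scales.

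The cost is wording and slightly more analysis work. Baseline values are already collected. If the log-link model is chosen, the result is a ratio and not a mean difference.

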### Participants and sample size justification

A total of 400 subjects will be recruited for the RCT. Based on an effect size of 0.3 (as reported in meta-analysis [33]), it has been determined that the sample size for each group should be 175 (i.e. 350 in total) to achieve 80% power in detecting a between-group difference via an independent t-test at a 0.05 significance level. Assuming an estimated 12.4% attrition rate (as reported in an RCT in a similar setting [41]), a total of 400 subjects (i.e. 200 subjects in each group) is necessary.

To be eligible for inclusion in the RCT, individuals must be (i) MSM, (ii) cis male, (iii) aged 18 or above, (iv) current dating app users, (v) HIV-negative, (vi) sexually active, and (vii) able to read and understand Chinese.

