### Randomisation and allocation concealment

After completion of the baseline questionnaire, participants will be randomly assigned to either the intervention group or control group via computer-generated block randomisation (with blocks of size 4) on a 1:1 randomisation ratio; no stratification will be applied. Participants will be automatically guided to the web content associated with their allocation.

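### The mixed model names only group as a covariate, so it returns one effect pooled over 3 and 6 months, and neither it nor the t-tests use the baseline outcome value by default

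*Protocol article*

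**What the plan says.** The Study outcomes section sets three measurement times: "The study outcomes will be measured in both groups at baseline (T0) and at 3 months (T1) and 6 months (T2) after baseline". The Randomisation section places the first of these before allocation: "After completion of the baseline questionnaire, participants will be randomly assigned".

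The Data analysis section begins with the two follow-ups: "The continuous outcomes in the intervention and control groups at the 3- and 6-month follow-ups will be evaluated using an independent t-test". The same sentence goes on to say that these outcomes are then "compared using a linear mixed-effects model with the intervention group as the covariate". On the random part it adds: "Subject as random effect will be included in the model if significant". Further covariates appear only in an additional analysis, and only for variables found to be imbalanced at baseline. Missing follow-up values are handled by a fixed rule: "The baseline-observation-carried-forward approach will be used for missing values at the 3- and 6-month follow-ups".

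No visit term, group-by-visit term or routine adjustment for the baseline outcome is mentioned. The text does not say that T0 rows enter the model.

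**The concern.** A random effect for subject needs more than one row per subject, so the visits have to be stacked. If group is the only fixed effect, a stacked model has a single treatment coefficient, and that coefficient averages over the visits in the data set. Two follow-ups were scheduled, but the plan's only longitudinal model cannot tell an effect that persists at 6 months from one that has faded by then.

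The plan also collects every outcome at T0 and then leaves that value out of both the t-tests and the main model, unless it happens to be imbalanced. At stake are the interpretability of the longitudinal result and precision that the trial could have from data it already collects.

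**Working it through.** **Inputs from the protocol article.** Standardised effect: "Based on an effect size of 0.3". Design target: "to achieve 80% power in detecting a between-group difference via an independent t-test at a 0.05 significance level". There are 175 per arm, 350 in total, and 400 after 12.4% attrition. The expected T0 difference is zero, because T0 precedes randomisation.

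**Assumed, not in the document.** Equal variances and equal correlation ρ between any two visits, with ρ = 0.3, 0.5 or 0.7; a two-sided test; a continuous outcome.

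**Step 1: the plan's own figure.** n = 2(1.96 + 0.842)²/0.3² = 174.5, so 175 per arm. Exact noncentral-t power at 175 is 79.9%. Attrition: 350/(1 − 0.124) = 399.5, so 400. Both figures reproduce. A one-sided test would give 138, so the plan is two-sided.

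**Step 2: what the group coefficient estimates.** With complete rows and equal correlations, each visit gets equal weight. Let d1 and d2 be the true differences at T1 and T2.

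| d1, d2 | T1+T2 rows: (d1 + d2)/2 | T0+T1+T2 rows: (0 + d1 + d2)/3 |
|---|---|---|
| 0.3, 0.3 | 0.30 | 0.20 |
| 0.4, 0.2 | 0.30 | 0.20 |
| 0.3, 0 | 0.15 | 0.10 |
| 0, 0.3 | 0.15 | 0.10 |

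Simulation of 4000 trials per scenario (ρ = 0.5, 200 per arm) agreed to within 0.002. The first two rows of the table cannot be told apart from the coefficient, nor can the last two.

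**Step 3: power at 175 per arm.** The noncentrality is d·√(175/2)/√v on 348 degrees of freedom, with two-sided alpha 0.05. Here v is the variance of the quantity compared, in units of the single-visit variance.

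| Analysis | d | v | ρ = 0.3 | ρ = 0.5 | ρ = 0.7 |
|---|---|---|---|---|---|
| One visit, unadjusted t-test | 0.3 | 1 | 79.9% | 79.9% | 79.9% |
| One visit, adjusted for T0 | 0.3 | 1 − ρ² | 83.5% | 89.8% | 97.5% |
| Group-only, T1+T2 rows | 0.3 | (1 + ρ)/2 | 93.5% | 89.8% | 85.9% |
| T1+T2 average, adjusted for T0 | 0.3 | (1 + ρ)/2 − ρ² | 96.2% | 97.7% | 99.7% |
| Group-only, T0+T1+T2 rows | 0.2 | (1 + 2ρ)/3 | 72.4% | 62.7% | 55.0% |

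Worked example at ρ = 0.5, one visit adjusted: v = 0.75, noncentrality = 0.3 × 9.354/0.866 = 3.24, power 89.8%.

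The gain comes from the baseline covariate. The visit terms make the 3- and 6-month contrasts readable; they do not add power.

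**The case against.** Four points on the other side carry weight.

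- **Visit-specific differences are already planned.** The t-tests supply them, and the sample size rests on a t-test. This stands. A reader might infer that the trial cannot estimate a 3-month or 6-month effect at all; that is true of the mixed model only. A pooled effect is also a legitimate quantity to report.
- **The T0 rows are hypothetical.** A reader might infer that the plan dilutes its effect by a third and loses power. The sentence takes the 3- and 6-month outcomes as its subject and never names T0 as an outcome row. On that reading there is no dilution, and pooled power exceeds the planned 80% at every correlation shown. The last row of the power table is a warning about an ambiguity, not a description of the plan.
- **Missing visits do not distort the group contrast through a time trend.** A reader might expect this when no visit term is fitted. The carry-forward rule fills every follow-up row, so the data are balanced and a visit main effect is unrelated to group.
- **This is a condensed article, and an unseen analysis plan could add the terms.** That is possible. But the article is not silent: it states the covariate, the random effect and the one circumstance in which more covariates enter. An analysis plan with visit and baseline terms would extend the published model, so the wording is worth settling.

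**Conclusion.** The point holds as a weakness in a stated model that is cheap to improve. As written, and on the natural reading, the mixed model gives one average of the 3- and 6-month differences and cannot separate them. The analyses that do separate them are unadjusted, and the baseline outcome is unused by default.

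Under the assumed correlations, baseline adjustment adds about 4, 10 and 18 percentage points to single-visit power, and about 3, 8 and 14 points to pooled power. These figures take the plan's effect of 0.3 at both follow-ups and 175 complete subjects per arm, and they leave aside any effect of carrying baseline values forward. If T0 rows were stacked, which the text does not say, the coefficient would be exactly one third below the mean follow-up effect, whatever the correlation. The sample-size figures are not affected.

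**What to change.** State the model as fixed effects for group, visit (T1, T2) and group-by-visit, with the T0 value of the outcome as a covariate. Say explicitly that T0 is not an outcome row. Report the between-group contrasts at 3 and at 6 months from this model and, if wanted, their average.

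The cost is a change of wording and a few extra parameters among 400 subjects; no new data are needed. There is one trade-off. A single-visit contrast, even adjusted for baseline, has less power than the group-only pooled effect when the correlation is low (83.5% against 93.5% at ρ = 0.3), the same at 0.5, and more at 0.7. Reporting the adjusted average beside the two visit contrasts keeps the advantage of pooling.

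### The subject random effect is kept only if a test finds it significant, so a pre-test can leave a man's 3- and 6-month reports analysed as independent; the effect on type I error is small but avoidable

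*Protocol article*

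**What the plan says.** Under Study outcomes, the protocol article sets the schedule: "The study outcomes will be measured in both groups at baseline (T0) and at 3 months (T1) and 6 months (T2) after baseline". Each man therefore supplies two post-baseline values for each outcome.

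Under Data analysis, continuous outcomes at the two follow-ups are first examined with independent t-tests, "then compared using a linear mixed-effects model with the intervention group as the covariate". The next sentence makes the subject term conditional: "Subject as random effect will be included in the model if significant". The test and its level are not stated, and no other within-subject correlation term is named. The same section handles missing follow-up values thus: "The baseline-observation-carried-forward approach will be used for missing values at the 3- and 6-month follow-ups".

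The sample size section bases the trial on a t-test: "Based on an effect size of 0.3", it requires 175 men per group "to achieve 80% power in detecting a between-group difference via an independent t-test at a 0.05 significance level".

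**The concern.** Two reports from the same man are correlated because of how the data are collected. That is a feature of the design and does not need to be established by a test. A non-significant variance component does not show that the correlation is zero; it may only show that the test lacked power.

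Under the stated rule a non-significant result removes the only random effect. What remains is an ordinary regression on two rows per man, treated as if they came from different men. The standard error of the group effect is then too small, and its p-value and confidence interval too favourable. The rule also lets the data choose the model, possibly differently for each outcome.

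This is a rule the article states, so it is not a detail left to an analysis plan.

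**Working it through.** **The plan's own figure.** With effect size 0.3, two-sided alpha 0.05 (sidedness is not stated, but two-sided reproduces the figure) and 80% power:

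n per group = 2 × (1.96 + 0.8416)² / 0.3² = 174.4, rounded up to 175.

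Allowing for 12.4% attrition: 350 / (1 − 0.124) = 399.5, so 400. The sample size reproduces. It rests on a t-test at one time point and does not involve the subject effect.

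**Effect of leaving the term out.** Let n be the men per group, sigma² the outcome variance and rho the correlation between a man's two reports.

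- True variance of the group difference, averaged over two visits: (2/n) × sigma²(1 + rho)/2 = sigma²(1 + rho)/n.
- Variance if the 2n rows per group are taken as independent: 2 × sigma²/(2n) = sigma²/n.
- The standard error is therefore too small by a factor sqrt(1 + rho).
- Actual type I error at nominal 5%: 2 × [1 − Phi(1.96 / sqrt(1 + rho))].

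**How often the term would be dropped.** The whole procedure (pre-test, then the chosen model) was simulated under no treatment effect, with 1,000,000 draws per scenario, a normal outcome, 200 men per group and no missing values. Because the article names no test, two pre-tests were tried: a one-sided 5% test of the variance component, and the harsher two-sided 5% cut-off. In the last three columns the first figure is for the one-sided pre-test and the second for the two-sided one.

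| rho (assumed) | Type I error if term always omitted (formula) | Term dropped | Type I error in trials that drop it | Type I error, all trials |
|---|---|---|---|---|
| 0.05 | 5.6% | 74% / 83% | 5.6% / 5.6% | 5.3% / 5.4% |
| 0.10 | 6.2% | 36% / 48% | 6.2% / 6.2% | 5.2% / 5.4% |
| 0.15 | 6.8% | 9% / 15% | 7.0% / 6.9% | 5.1% / 5.2% |
| 0.20 | 7.4% | 0.8% / 1.9% | 7.9% / 7.9% | 5.0% / 5.0% |
| 0.30 | 8.6% | about 0% | too few to estimate | 5.0% |

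With 350 men and the one-sided pre-test, the drop rates at rho 0.05, 0.10 and 0.15 are 76%, 41% and 12%. Keeping the term in every trial gave a type I error of about 5.0% at every rho tried, from 0 to 0.5.

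**Effect of carrying baseline forward.** A man who misses both visits has identical 3- and 6-month values. As an upper case, suppose all of the assumed 12.4% attrition is of this kind and the variance is the same throughout. The correlation in the analysed data is then 0.124 + 0.876 × rho:

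- rho 0.05: 0.124 + 0.044 = 0.168
- rho 0.10: 0.124 + 0.088 = 0.212
- rho 0.15: 0.124 + 0.131 = 0.255

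Simulation of this case with the harsher cut-off gives drop rates of about 11%, 2% and 0.1%, with overall type I error near 5%. If fewer men miss both visits, the drop rates lie between these and the table's.

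**The case against.** The strongest reply is that the pre-test largely protects against the harm it could cause. Where the correlation is large enough to matter, 400 men nearly always make it significant; where the term is dropped, little is lost. This stands, and it limits the size of the point.

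Four stronger readings are tempting, and the documents do not support them.

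- **A false-positive rate of 7% to 11%.** The formula gives 7.4% at rho 0.2 and 11.0% at rho 0.5, but only if the term is left out. Under the stated rule that happens in 1% to 2% of trials at rho 0.2 and practically never at 0.3 or above.
- **The powered comparison depends on the rule.** The sample size is based on an independent t-test, and t-tests done separately at each visit do not use the subject term.
- **A change-over-time contrast is also distorted.** None is planned: intervention group is the only covariate named, with no time or group-by-time term.
- **Rare outcomes such as chemsex and group sex are at much greater risk.** The article gives neither a distribution nor a correlation for its outcomes. Checks with assumed skewed distributions dropped the term more often than with normal data, yet overall type I error stayed at or below about 5.5%. The tables above assume normality and cannot settle this further.

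The reply does not justify the rule. It shows that the rule does little damage, but gives no reason to prefer it to always keeping the term.

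**Conclusion.** The point holds as a minor fault of specification. The article makes the only within-subject correlation term depend on a significance test, and a non-significant result leaves paired reports analysed as independent.

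With 400 men and normal outcomes, this happens mainly at rho below about 0.15. It raises type I error to about 5.5% to 7% in the trials affected and to at most about 5.4% overall. Carrying baseline forward lowers the chance of dropping the term.

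These figures rest on an assumed rho, an assumed 5% pre-test and normality, none of which the article supplies. Neither the by-visit t-tests nor the planned 400 men are called into question.

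**What to change.** Replace the conditional sentence under Data analysis with: *A subject random intercept will be included in the linear mixed-effects model for every outcome, regardless of its statistical significance.*

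This names one structure for all outcomes and leaves nothing to be decided from the data. It costs one sentence, needs no additional men, and held type I error at about 5.0% at every correlation examined.

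### Adjusting each outcome's main model for its own baseline value, instead of adjusting only for variables found imbalanced, would gain precision at almost no cost

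*Protocol article*

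**What the plan says.** The Study outcomes section fixes the timing: "The study outcomes will be measured in both groups at baseline (T0) and at 3 months (T1) and 6 months (T2) after baseline". Allocation comes after completion of the baseline questionnaire, in blocks of 4 and without stratification, according to the section on randomisation. The baseline value of each outcome is therefore a pre-randomisation measurement.

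Under Data analysis, continuous outcomes at 3 and 6 months are first examined by independent t-test and then "compared using a linear mixed-effects model with the intervention group as the covariate". No baseline term is named in either step. Adjustment is conditional: "In case of a baseline imbalance, additional analysis will be performed, with adjustment of the variables found to be imbalanced". No covariate is named in advance, and no criterion for imbalance is given. The only other use of the baseline outcome in that section is to fill in missing follow-up values.

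**The concern.** Past behaviour, asked with the same item over the same 3-month window, is a natural candidate for a strong predictor of later behaviour. A main model without it leaves that variation in the error term, although the data are already collected.

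The trigger is a separate weakness. After proper randomisation, any baseline difference is chance. A covariate is useful because it predicts the outcome, not because it happens to differ between arms. A rule based on observed imbalance can adjust for a variable of no prognostic value and leave out a strong one. With no list and no criterion, it is settled only once the data are seen whether an adjusted result exists and which one it is. Two answers to the primary question may then stand side by side, with no rule in the article on which to emphasise.

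Both points rest on what the article states, not on a detail left to a fuller plan. An analysis plan that prespecified baseline adjustment in the main model would have to change this text.

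**Working it through.** **Inputs from the protocol article (Participants and sample size justification).** Effect size: "Based on an effect size of 0.3 (as reported in meta-analysis [33"). Size: "the sample size for each group should be 175 (i.e. 350 in total"). Test: "to achieve 80% power in detecting a between-group difference via an independent t-test at a 0.05 significance level". Attrition: "Assuming an estimated 12.4% attrition rate". Total: "a total of 400 subjects (i.e. 200 subjects in each group) is necessary".

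**Input not in the documents.** The correlation r between baseline and follow-up. It is assumed, and a range is shown.

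**Step 1: reproduce the plan's figure.** Normal approximation, two-sided 0.05, 80% power:

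n per arm = 2 × (1.960 + 0.842)² / 0.3² = 174.4, rounded up to 175.

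The exact t calculation gives 175.4, and noncentral-t power at 175 per arm is 79.9%. A one-sided test would need only 138, so the plan is two-sided. Attrition: 350 / (1 − 0.124) = 399.5, rounded up to 400. The stated figures reproduce, and they take no credit for baseline adjustment.

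**Step 2: add linear adjustment for baseline.** The residual variance becomes (1 − r²) times the original, so the effect in residual SD units is 0.3 / √(1 − r²). The equivalent unadjusted sample size is 175 / (1 − r²) per arm. Noncentral-t power at 175 per arm:

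| Assumed r | 1 − r² | 0.3 / √(1 − r²) | Power | Equivalent n per arm |
|---|---|---|---|---|
| none (as planned) | 1 | 0.300 | 79.9% | 175 |
| 0.2 | 0.96 | 0.306 | 81.5% | 182 |
| 0.3 | 0.91 | 0.314 | 83.5% | 192 |
| 0.4 | 0.84 | 0.327 | 86.3% | 208 |
| 0.5 | 0.75 | 0.346 | 89.8% | 233 |
| 0.6 | 0.64 | 0.375 | 93.8% | 273 |

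**Step 3: check what the trigger does to error rates.** Simulation with 175 per arm, normal data, no treatment effect, 40,000 trials per r, the baseline outcome as the only covariate, and imbalance flagged at p < 0.05 (an assumed criterion, since the article gives none):

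| Null rejection rate | r = 0.3 | r = 0.5 | r = 0.7 |
|---|---|---|---|
| Unadjusted test, all trials | 5.1% | 5.2% | 4.9% |
| Either analysis positive (adjusted one run only if flagged) | 5.2% | 5.3% | 5.0% |
| Switch to the adjusted result if flagged | 4.8% | 4.5% | 3.4% |
| Unadjusted test, flagged trials only | 10% | 18% | 34% |
| Adjusted test, flagged trials only | 5% | 4% | 5% |

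Overall error stays near or below 5% under every reading of the rule. The difference appears only within the roughly 5% of trials that show a significant baseline imbalance in the outcome. There the unadjusted result is unreliable and the adjusted one is not.

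**The case against.** The strongest reply is that nothing here is wrong on the plan's own terms. In a randomised trial the unadjusted comparison is valid. The sample size was computed for the same t-test, and 175 per arm reproduces the stated 80%. The power given up is relative to a more efficient analysis that the plan did not choose. This stands, and it makes the point an improvement rather than a correction.

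Stronger readings that a reader might infer are not supported:

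- *The trigger inflates type I error or replaces the primary answer.* The article calls the adjusted analysis additional, and Step 3 shows hardly any inflation with one covariate. What remains is room for selective emphasis.
- *Covariates are chosen after unblinding.* The Study design section describes a non-blinded trial, so there is no unblinding event, and nothing is said about the analyst. The sound form is that the choice follows sight of the data.
- *Nothing guards against chance imbalance.* With 200 per arm, the standard error of a standardised baseline difference is √(2/200) = 0.10, so large imbalances are uncommon, and the trigger itself would adjust for the baseline outcome if it were flagged.
- *A large power gain is assured.* The correlation is unknown. For a self-reported 3-month frequency that may be skewed, it could be low, and at 0.2 or 0.3 the gain is only about 2 to 4 points.
- *Baseline is never missing.* Randomisation follows completion of the questionnaire, but the article does not say that every item is mandatory.

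The sentence on the mixed model may also be a condensed covariate list, since it names no visit term either. That has some force, but it does call group the covariate, and the imbalance rule is stated outright.

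**Conclusion.** The point holds as a nearly free improvement. The planned comparison is valid and consistent with the sample-size calculation, but it leaves unused a pre-randomisation measurement of every outcome, and its only route to adjustment selects covariates by chance imbalance.

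The gain is about 2 points of power at r = 0.2, 6 at 0.4, 10 at 0.5 and 14 at 0.6. These figures assume a linear model with an untransformed baseline, an effect of 0.3 and 175 analysed per arm. They do not carry over exactly to a log-transformed baseline or to the planned analysis of all 200 per arm with baseline values carried forward. The cost of the trigger is not a higher overall error rate. It is a misleading main result in the few trials with a marked imbalance, and freedom over which result to stress.

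**What to change.** Replace the sentence on baseline imbalance in the Data analysis section with:

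> The main model for each outcome will include the baseline value of that outcome as a pre-specified covariate (suitably transformed, e.g. log(baseline+1), for counts), whatever the observed balance; no covariate will be selected by observed baseline imbalance.

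Any further prognostic covariates should be named in the same place before the data are seen. The change needs no new data and no more participants. It has two small costs: an isolated missing baseline item needs a simple handling rule, and the adjusted model, not the t-test, becomes the main analysis. The sample size can stay as it is.
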